### Economic evaluation

We will measure costs and assess cost-effectiveness from both a health service and a societal perspective. To calculate the cost of TCBT, the number of sessions with therapists will be recorded and combined with the unit cost of therapist time. The latter will be calculated using information on the salary band of therapists, with additional costs representing capital, overheads, training and qualifications.^44^ We will ask therapists to estimate how much time during a typical working week is spent in telephone contact with patients, and combine this with the total cost and total hours worked per week, in order to produce a cost per hour of direct patient contact time. For WBCBT, the number of times therapist support is provided will be recorded and costed in a similar way. The WBCBT development costs will be estimated and apportioned over those using the intervention. Other service use will be measured with a service receipt schedule at baseline (going back 6 months) and at each follow-up (with measurement covering the whole period since the prior interview). The schedule will be based on other questionnaires used in similar research.^29^ Services will include primary and secondary healthcare, and medication. Service costs will be generated by combining these data with appropriate unit cost information (eg, NHS Reference Costs,^44^ and the British National Formulary) and these costs added to the intervention costs in order to generate total health costs per person.

Societal costs will be calculated by including family care costs and lost production. Family care costs will be recorded by asking patients to state how much time per week family members (and friends) spent providing support in specific areas *because of the IBS*. This time will be combined with average wage rates. Lost days and hours from work will be recorded on the schedule and combined with average wage rates to generate lost production costs. Cost comparisons between the three groups will be made at 3, 6 and 12 months, and over the entire follow-up period, in both cases, controlling for baseline costs. Cost data are usually skewed and cost comparisons will use a bootstrapped regression model to generate appropriate 95% CIs around the cost differences.

Cost-effectiveness will be assessed (from health and societal perspectives) by combining the cost data with the change score on the IBS-SSS, WASAS and QALYs. The latter will be generated from the EQ-5D combined with UK-specific tariffs. Area under the curve methods, controlling for baseline utility, will be used to calculate the number of QALYs accrued over the follow-up period. If outcomes are better for one group compared to another and costs are lower, then it will be defined as being ‘dominant’. If outcomes are better and costs are higher, an incremental cost-effectiveness ratio will be generated to indicate the extra cost incurred to achieve an extra point reduction in symptoms or extra QALY. Cost-effectiveness planes will be produced, using 1000 cost and outcome differences (from bootstrapped regression models) for each 2-way comparison, to explore the uncertainty around the results. Cost-effectiveness acceptability curves will also be produced using bootstrapped regression models with net benefit values as the dependent variables. The net benefit approach requires an assumption about the value placed on a unit improvement in outcome. For QALYs, a range from £0 to £60 000 will be used, thus including the threshold thought to influence NICE decisions. For the IBS-SSS and WASAS, there are no accepted thresholds, so a range will be chosen such that the points at which one intervention has a 60%, 70%, 80% and 90% likelihood of being the most cost-effective option can be identified.

Sensitivity analyses will be conducted by changing the intervention costs upwards and downwards by 50%, using minimum wages to value lost production, family care and travel time, and by also using the replacement cost approach to value family care with the cost of a homecare worker used a shadow price.

Modelling beyond the trial period and making comparisons with other interventions is not in the scope of this project.

## Ethics and dissemination

### Ethical issues

The trial will be conducted in full accordance with current guidelines for ethical research conduct. The study will be performed subject to Research Ethics Committee (REC) approval, including any provisions of Site Specific Assessment (SSA), and local Research and Development (R&D) approval.

The potential benefit to participants from the interventions in this study is a greater understanding of their IBS, an improved ability to manage their condition and possibly reduced symptom severity or impact on their life from their IBS. This may lead to societal benefits such as a reduction in work days lost and reduced use of NHS resources. The risks of undertaking CBT are minimal; undertaking the sessions will require a time commitment on behalf of the participants, and focusing on their IBS symptoms could temporarily worsen the symptoms in the short term. The CBT is provided alongside usual care so the participants will still have access to all usual NHS services. Participants will be fully informed of the trial procedures before entering the study via a Patient Information Sheet, and any questions will be answered by the research team prior to signing the on-line consent form.

#### Fair access to the study

Participants need to have web access, which could exclude some people who would otherwise like to take part. However, three quarters of households have web access, this figure is rapidly increasing, and those without home access can use public computers (eg, local library).

Participants aged over 60 years are required to have undergone a consultant review to exclude other serious causes of their bowel symptoms in the last 2 years, because colorectal cancer is more common in those aged over 60 years and guidelines recommend that changes in bowel habit in this group require hospital tests beyond the scope of this trial.

To maximise recruitment and to ensure that motivated patients are not excluded from treatments that may help, participants in the TAU-alone group will be given access to the Regul8 website at the end of the trial.

### Dissemination

The results of this study will be communicated to participants at study end and disseminated via peer reviewed publications and conference presentations. The results will enable clinicians, patients and health service planners to make informed decisions regarding the management of IBS with CBT.

### Service users

IBS patients and the IBS network, a patient self-help group, have been involved in providing feedback for the design of the MIBS^14^ trial (in which the Regul8 website used in this study was developed and piloted). Patients were substantially involved in the website design with service users, working through each on-line module during development and providing ‘Think Aloud’ feedback to inform the design. Participants from the MIBS trial have also provided input and feedback on the proposals for this research. Two participants are now PPI representatives for this study, providing ongoing input (both informal feedback and participating in Trial Steering Committee (TSC) and research meetings) to ensure it addresses issues relevant to users.

### Research governance

This study will be conducted in accordance with the International Conference for Harmonisation of Good Clinical Practice (ICH GCP) guidelines, and the Research Governance Framework for Health and Social Care. The University of Southampton is the Sponsor for this study.

A Trial Steering Committee (TSC) will oversee the trial procedures and ensure good conduct of the study; they will meet at least annually. Observers from the HTA will be invited to all TSC meetings.

A Data Monitoring and Ethics Committee (DMEC) will oversee the trial data and ethics, with an independent chair and at least two independent members, and a Patient and Public Involvement Representative, along with the lead investigator (HE), with the support of the TSC. They will meet at least annually.

Regular updates and meetings will ensure good communication. The collaborators will hold meetings at least four times a year. The research assistant will circulate a monthly update to review progress relative to the project plan, highlighting any issues that need to be addressed. Each team member will consult the other team members immediately by email and/or phone on any issues that arise.

### Monitoring and audit

The study will be monitored and audited in accordance with Southampton University procedures. All trial related documents will be made available on request for monitoring and audit by the University of Southampton, the relevant REC and other licencing bodies.

### Safety

#### Adverse events

AE are any clinical change, disease or disorder experienced by the participant during their participation in the trial, whether or not considered related to the use of treatments being studied in the trial.

#### Serious adverse events

An AE is defined as serious (an SAE) if it results in one of the following outcomes
A life-threatening AEIn-patient hospitalisationA disability/incapacityA congenital anomaly/birth defect in the offspring of a subjectOther medical events requiring intervention to prevent one of the above outcomes.

#### Serious adverse reactions

A serious adverse reaction (SAR) can be defined as: A SAE considered to be a reaction to one of the supplementary therapies.

#### Reporting serious adverse events and reactions (SAEs and SARs)

On completion of an SAE, the chief investigator will assess whether the SAE is a SAR or a (SUSAR). A SUSAR is any adverse reaction that is classed as serious and is suspected to be caused by the intervention, and is not expected. If the SAE is classified as a SUSAR, the trial team will report the SUSAR to the EC. For a SUSAR that is fatal or life-threatening, the team, on behalf of the sponsor, has 7 days to report the SUSAR to the EC. For a SUSAR that is not fatal or life-threatening, the team has 15 days to report. The SUSAR is recorded in the participant’s medical notes and the participant will be followed up.

#### Follow-up after AEs

After a SAE or SAR, a decision will be made by the trial team, after advice from the relevant authorities and the participant's GP, as to whether the participant should be withdrawn from either their randomised treatment or from the trial. Arrangements will be made by the trial team for further assessment and management as agreed with the relevant authorities, GP and participant. The investigator will provide the trial team with a 1-month follow-up report on all SAEs and SARs. Further monthly reports should be provided in the absence of resolution. These reports will be communicated to the TSC, DMEC and MREC, and to the local R&D office. Blank Adverse Event Forms will be distributed to sites that are recruiting, and therapists and patients will be prompted to self-report SAEs in the follow-up questionnaires.

#### AEs that do not require reporting

Expected AEs include planned/elective hospitalisations, and these will not be collected as SAEs.

### Stopping rules

The trial may be prematurely discontinued by the Sponsor or Chief Investigator on the basis of new safety information or for other reasons given by the Data Monitoring & EC, Trial Steering Committee, Regulatory Authority or EC concerned.

The trial may also be prematurely discontinued due to lack of recruitment or on advice from a Trial Steering Committee (if applicable), who will advise on whether to continue or discontinue the study and make a recommendation to the sponsor. If the study is prematurely discontinued, active participants will be informed and no further participant data will be collected.

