### Target population

*Inclusion Criteria*: Adults (18 years and over) with refractory IBS. Refractory IBS is defined for this study as fulfilling the ROME III criteria for IBS^15^ and reporting ongoing clinically significant symptoms determined by a IBS symptom severity score (IBS-SSS) of 75 or more. Patients need to have been offered first-line therapies (eg, antispasmodics, antidepressants or fibre based medications) and have continuing IBS symptoms for 12 months or more. Potential participants aged over 60 years will only be included if they have had a consultant review in the previous 2 years to confirm that their symptoms are related to IBS and that other serious bowel conditions have been excluded. This is because there is an increased risk of bowel cancer in the over 60 years’ age group and clinical guidance suggests further investigations should be undertaken in this group.^4^

*Exclusion criteria*: Unexplained rectal bleeding or weight loss, diagnosis of inflammatory bowel disease, coeliac disease, peptic ulcer disease or colorectal carcinoma. People unable to participate in CBT due to speech or language difficulties or those with no access to an internet computer to be able to undertake the WBCBT or who have received CBT for IBS in the past 2 years, and those who have had previous access to the Regul8 website or who are currently participating in an IBS/intervention trial.

*Withdrawal criteria*: Participants will be withdrawn from the trial if there are any concerns regarding informed consent. Participants can also withdraw if they choose, without giving a reason. If a participant withdraws consent for research follow-up during the trial, the trial team will be informed. Information will be collected in the Drop-out Report Form and, where possible, reason for drop out will be recorded.

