### Adherence to therapy

Patients’ adherence to the treatments will be measured through recording the number of phone sessions and an automated count of web sessions accessed. Completing four or more sessions of the website and one or more of the telephone support calls will be deemed as compliant with the website. In the TCBT arm, completing four or more of the initial telephone CBT sessions will be deemed as compliant.

Any modifications or departures from randomised treatments, and withdrawal of participants from trial treatment or research follow-up, will be recorded and reported as such.

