### Statistical analysis

The Statistical analysis plan has been approved by the trial steering committee. The aim is to evaluate effectiveness, and all analyses will follow the intention-to-treat principle. Group differences on the primary IBS-SSS outcome will be assessed using a mixed linear regression model for repeated measurements. In this model, IBS-SSS at post-treatment time points (3, 6 and 12 months) will feature as the dependent variable. Explanatory variables will be baseline IBS-SSS, treatment group, IBS symptoms type, stratifier (centre) and time and time by treatment interaction terms to allow for different group differences at the various assessment time points. (The assessment time point of primary interest is 12 months. The modelling provides the treatment effect estimates at the 12 month time point as well as for further post-treatment secondary time points). Correlation between repeated measures of the same participant or between participants, or due to sharing the same therapist, will be allowed for by including subject-varying random intercepts as well as therapist-varying random intercepts for TCBT and WBCBT groups in the mixed models. Mixed models account for missing outcome data under the missing at random assumption. The effect of departures from this assumption will be checked using sensitivity analyses.^42^ WASAS scores will be analysed using mixed models in a manner similar to the analysis of IBS-SSS. Secondary outcomes, including Subjects’ Global assessment of relief (SGA), EQ-5D, Enablement, HADS, Brief Illness perception Questionnaire (IPQ), Cognitive Scale for Functional Bowel disorders, The Belief about Emotions Scale (BES), The “Impoverished Emotional Experience (IEE)” factor of the Emotional Processing Scale, The Positive and Negative Affect Schedule (PANAS), adverse events (AEs) and healthcare utilisation, are important to measure the wider IBS effects and will be analysed similarly (as appropriate for continuous or dichotomous outcomes). A complier average causal treatment effect will be estimated using instrumental variable methods to assess efficacy if there is appreciable lack of compliance.^43^

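### Ending all data collection after any early stop, even one for poor recruitment, would forgo the 12-month primary outcome of patients already randomised

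*Protocol article*

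**What the plan says.** **Early stop.** Stopping rules (under Safety) allows the trial to end on new safety information or for reasons given by the committees or authorities. It then adds a ground unrelated to safety: "The trial may also be prematurely discontinued due to lack of recruitment or on advice from a Trial Steering Committee (if applicable"). One unqualified sentence covers all of these: "If the study is prematurely discontinued, active participants will be informed and no further participant data will be collected". Patients already randomised are not excepted.

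**Primary outcome.** Statistical analysis says "The assessment time point of primary interest is 12 months" and "all analyses will follow the intention-to-treat principle". The model is a repeated-measures mixed model on the 3, 6 and 12 month scores. It assumes missing at random, and sensitivity analyses are planned.

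**How outcomes are collected.** Under Data collection and Outcome measures, participants complete questionnaires online after automated email reminders. Staff telephone only those who do not respond.

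**Withdrawal.** Three sections bear on it:
- Target population lists consent concerns ("Participants will be withdrawn from the trial if there are any concerns regarding informed consent") and the participant's own choice.
- Adherence to therapy treats the two kinds of withdrawal as distinct: "withdrawal of participants from trial treatment or research follow-up, will be recorded and reported as such".
- Follow-up after AEs has the trial team decide, after a serious adverse event or reaction, "as to whether the participant should be withdrawn from either their randomised treatment or from the trial".

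**The concern.** A stop for slow recruitment is a reason to stop randomising. It is not a reason to stop sending an online questionnaire to people who have consented and been treated. A stop for safety is when later observation is most useful. Yet the rule, followed as written, ends collection in both cases, and a 12-month score not collected at 12 months cannot be recovered later.

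The rule also fits poorly with the protocol's own safety follow-up. Follow-up after AEs asks for a report at one month on every serious event, with further monthly reports until it resolves, and relies partly on patients reporting events in the follow-up questionnaires. The section on reporting serious events says a participant with a SUSAR will be followed up. Read literally, an early stop would cut these off.

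At stake, if the trial stops early, are the precision of the primary comparison and the later safety record. A smaller, separate matter is that the post-event withdrawal decision allows removal from the trial itself, on a ground not listed among the withdrawal criteria.

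**Working it through.** **1. The plan's own sample size (Proposed sample size).** Inputs: difference 35, SD 76, two-sided 2.5%, power 90%. The exact t calculation gives 119 per group, as stated. The adjustment factors also reproduce:
- therapists: 1 + (17 − 1) × 0.02 = 1.32
- baseline correlation: 1 − 0.4² = 0.84
- attrition: 1/(1 − 0.20) = 1.25

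119 × 1.32 × 0.84 × 1.25 = 164.9, so 165 per group and 495 in total. This figure is not in dispute.

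**2. Patients without a 12-month outcome at an early stop.** Recruitment plans 495 over 22 months: 495/22 = 22.5 per month. Assume constant accrual at rate r. At month m (12 ≤ m ≤ 22), r × m patients are randomised, at most r × (m − 12) have reached 12 months, and 12r have not. The fraction without the outcome is 12r/(r × m) = 12/m, whatever r is.

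| Stop at month | Randomised | Reached 12 months (at most) | Not reached | Fraction |
|---|---|---|---|---|
| 12 | 270 | 0 | 270 | 100% |
| 16 | 360 | 90 | 270 | 75% |
| 18 | 405 | 135 | 270 | 67% |
| 22 | 495 | 225 | 270 | 55% |
| 28 | 495 | 360 | 135 | 27% |
| 34 | 495 | 495 | 0 | 0% |

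After month 22 recruitment is complete and the number falls by 22.5 a month to zero at month 34.

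**3. Illustrative power for a month-18 stop.** With 20% attrition, analysed patients per arm are 135/3 × 0.8 = 36 (completers only) or 405/3 × 0.8 = 108 (all followed to 12 months). Let D₁ and D₀ be the design factors in the therapy and TAU arms. Then SE = 76 × √(0.84 × (D₁ + D₀)/n) and power = Φ(35/SE − 2.241).

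| Treatment of therapist clustering | n = 36 | n = 108 |
|---|---|---|
| 1.32 in both arms, as in the plan | SE 18.9, power 35% | SE 10.9, power 83% |
| 1.32 in the therapy arm only | SE 17.7, power 40% | SE 10.2, power 88% |
| Recomputed for 10 therapists, therapy arm only | SE 16.6, power 45% | SE 9.9, power 90% |

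In the last row, D₁ = 1 + (3.6 − 1) × 0.02 = 1.05 for n = 36 and 1 + (10.8 − 1) × 0.02 = 1.20 for n = 108.

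**4. What the completers-only figure leaves out.** At month 18, up to 22.5 × 12 = 270 patients would have reached 6 months and 22.5 × 15 ≈ 337 would have reached 3 months. Their scores enter the mixed model, so the power actually available is above the completers-only figure, by an amount that depends on correlations the article does not give.

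**5. Withdrawal after a serious event.** The documents give no event rate. Starting from the plan's 165 × 0.80 per arm, with 1.32 and 0.84 applied to both arms, power is 90.5%. An assumed extra loss of 1%, 2% or 5% lowers it to 90.1%, 89.7% or 88.5%. The effect on precision is small; the question is whether loss that follows a health event, by team decision, could bias the comparison.

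**The case against.** **The rule is contingent.** It has no effect if the trial runs as planned, and the article gives no likelihood of an early stop. This stands, and it limits the weight of the point.

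**The illustration uses on-plan accrual.** A trial recruiting 22.5 a month would not be stopped for poor recruitment. With slower accrual the counts fall and so does the power from following everyone. This also stands, which is why the fraction 12/m is the sturdier figure. At half the planned rate, for example, a month-18 stop has 202.5 randomised and 67.5 at 12 months, or 18 and 54 analysed per arm. The three clustering treatments then give power of about 18–23% against 51–62%. The ratio of patients is unchanged, and the gain from continuing remains large.

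**A reader might infer that collected outcomes are thrown away, or that intention to treat is broken.** The text supports neither. It says only that no more data will be gathered; nothing says existing data are deleted or excluded, and Storage of records retains the source documents. Ending collection on one calendar date truncates all three arms alike. That costs precision, but it excludes no randomised patient from the analysis on the basis of treatment received or outcome.

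**A reader might also infer that unblinded staff can remove patients after a serious event and so end their questionnaires.** That goes too far. The decision is case by case and follows advice from the authorities and the GP. Nothing says that research assistants take it, or that questionnaires then cease. What remains is that the section contrasts randomised treatment with the trial, while Target population lists no such ground for withdrawal.

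**Conclusion.** The point holds in a limited form. Stopping rules states a positive rule, not an omission that a fuller document could be expected to fill. Followed exactly, it forgoes the 12-month primary outcome of every randomised patient still short of 12 months: 12/m of them for a stop at month 12 to 22, and about 270 at the planned rate. For a month-18 stop at planned accrual, completers-only power is about 35–45%, against about 83–90% with full follow-up. This assumes constant accrual, 20% attrition and the plan's SD, difference and baseline correlation, and it ignores the part that the 3 and 6 month data recover under missing at random.

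It is an avoidable loss of precision and later safety data, conditional on an early stop. The planned sample size and the analysis of a completed trial are unaffected. The withdrawal wording is a secondary matter of consistency, with little effect on power at the loss rates assumed.

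**What to change.** **Stopping rules.** Replace the sentence so that, if recruitment or the trial stops early, patients already randomised continue the 3, 6 and 12 month questionnaires and safety reporting. The exceptions should be a participant's withdrawal of consent, concerns about consent as in Target population, or a direction from the ethics committee or sponsor for a stated reason.

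**Withdrawal.** Reconcile Target population, Adherence to therapy and Follow-up after AEs. They should agree on the grounds for withdrawal from the trial and state that a decision about treatment does not by itself end outcome collection. Adherence to therapy already separates treatment from research follow-up, so the terms exist. Whether any participant should stop treatment is not part of this change.

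**Cost.** A few sentences of protocol wording and, after an early stop, up to 12 months of the existing and mostly automated follow-up, with some telephone chasing of non-responders. The change has to be made before any stop.
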